## Figures and Tables

**Figure 1 healthcare-14-00323-f001:**
[figure not shown]
DiverAcción Intervention and timeline of the different phases of the study.

**Figure 2 healthcare-14-00323-f002:**
[figure not shown]
Feasibility Assessment of DiverAcción Digital ADHD Intervention: Measurement Model and Key Metrics.

**Figure 3 healthcare-14-00323-f003:**
[figure not shown]
CONSORT Flow Diagram Adapted for Feasibility Trials. It will be completed after the collection.

**Table 1 healthcare-14-00323-t001:** DiverAcción Program Structure by Target Group.

Dimension	Frequency	Main Aim	Description	Administered To
Collaborative Agenda	Daily (7 days/week)	Promote planning and monitoring in natural contexts	Participants co-design a personal agenda to schedule daily activities, prioritize tasks, estimate duration, and monitor completion.	Children/Adolescents
Training Sessions	12 sessions (2/week, 45 min each, 6 weeks)	Develop executive skills and emotional regulation through gamified tasks	Virtual sessions focused on planning, organization, time management, and emotional self-regulation using interactive exercises.	Children/Adolescents
Psychoeducation Sessions	6 sessions (1/week, 45 min each, 6 weeks)	Support generalization and caregiver mediation	Sessions for parents and teachers to reinforce strategies, manage routines, and reduce stress.	Parents/Teachers
Therapeutic Support	Continuous (chat/email) + 2 videoconferences (weeks 1 and 3)	Provide guidance and resolve doubts	Integrated communication tools and scheduled videoconferences to monitor progress and address questions.	Children/Adolescents & Parents/Teachers

**Table 2 healthcare-14-00323-t002:** Variables, instruments and timing of administration.

Variables	Instruments	Time Data Collection	Administered to:
Previous experience with digital interventions, sociodemographic, educational and economic data of children and adolescents, pharmacological treatment, other behavioral or psychoeducational interventions	interview	T0	Parents
Preferences regarding digital intervention format	interview	T0	Children and Adolescents
Symptom severity in inattention, hyperactivity–impulsivity and oppositional behaviors (not for subtype classification)	SNAP-IV	T0	Parents
Therapeutic attitudes of professionals towards technology	e-TAP-T	T0	Teachers Occupational therapists
IQ estimated	WASI-II	T0	Children and Adolescents
Feasibility	Automated metrics recorded by the platform: adherence, number of uses, sessions, time of use, errors	T1	Children and Adolescents Parents Teacher Occupational Therapists
Acceptability	TAM questionnaire	T1	Children and Adolescents Parents Teacher Occupational Therapists
Usability	SUS	T1	Children and Adolescents Parents Teacher Occupational Therapists
User-friendly design	Visual analog scale from 1 to 10	T1	Children and Adolescents Parents Teacher Occupational Therapists
Participant satisfaction	Participant Satisfaction Questionnaire	T1	Children and Adolescents Parents Teacher Occupational Therapists
Therapeutic Alliance	WAI-I	T1	Children and Adolescents
Executive functioning	BRIEF-2 for parents and teachers TEXI Inventory	T0, T1, T2	Parents and Teachers Children and Adolescents
Time management of children and adolescents	Time-S questionnaire EMT	T0, T1, T2	Children and Adolescents Teachers
Prospective Memory	PRMQ-C Automated metrics recorded by the platform	T0, T1, T2 T1	Children and Adolescents
Emotion regulation strategies in everyday life	ERQ-CA	T0, T1, T2	Children and Adolescents
Health-related quality of life (HRQoL)	KIDSCREEN-52	T0, T1, T2	Children and Adolescents
Parents’ perceptions of their parenting competence	BPSES	T0, T1, T2	Parents
Parental stress levels	PSI-4-SF	T0, T1, T2	Parents

Note: T0 = baseline, T1 = immediately post-intervention, T2 = 3 months after intervention.

**Table 3 healthcare-14-00323-t003:** Progression Criteria for Feasibility Outcomes.

Domain	GO (Proceed)	AMEND (Modify)	STOP (Do Not Proceed)
Recruitment	≥70% of eligible approached	50–59%	<50%
Retention	≥80% at T1/T2	60–79%	<60%
Data completeness	≥80% completeness	70–79%	<70%
Adherence	≥80% agenda & training; 100% videoconferences	60–79% agenda/training	<60% agenda/training
Fidelity	≥80% protocol elements delivered	60–79%	<60%
Acceptability (TAM)	Mean ≥ 3.5	Mean 3.0–3.49	Mean < 3.0
Usability (SUS)	Score ≥ 68	Score 60–67	Score < 60
Dropouts	≤20% dropout rate	21–29% dropout rate	≥30% dropout rate

Note. GO = criteria met for progression to definitive trial; AMEND = criteria met with modifications; STOP = criteria not met. Predefined success thresholds were based on widely used benchmarks in feasibility research, such as ≥80% session completion [69], SUS ≥ 68 [55], and TAM mean ≥ 3.5 [70].

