### 2.7. Sample Size

The planned sample size is 30 children/adolescents. This number is considered adequate for feasibility and usability studies in children and adolescents [25,51], ensuring sufficient variability to identify barriers and facilitators without requiring a formal calculation of statistical power [52]. This study was designed as a pilot trial aimed at assessing the feasibility and acceptability of the intervention. The sample size (n = 30) is considered appropriate for feasibility objectives, as it allows for the evaluation of implementation aspects, adherence, usability, acceptability and participant satisfaction. However, this sample size is insufficient to establish the efficacy of the intervention; Therefore, the findings should be interpreted as preliminary and intended to inform the design of future randomized controlled trials with larger samples.

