#### 2.9.2. Feasibility Outcomes

The primary aim of this study is to assess feasibility across multiple domains, following established frameworks for pilot and feasibility trials [52,67,68]. Progression criteria for feasibility outcomes are summarized in Table 3 and Figure 2.

The following outcomes will be evaluated:

*Recruitment and Retention*

Recruitment will be measured as the proportion of eligible participants who consent to participate, and the average recruitment rate per month. Retention will be defined as the percentage of participants who complete all planned assessments at T1 (post-intervention) and T2 (follow-up).

*Data Completeness and Missing Data*

Data completeness will be calculated as the proportion of participants providing valid data for each measure at each time point. Patterns and reasons for missing data will be documented. This information will inform the feasibility of data collection procedures and guide refinements for a future trial. Primary feasibility analyses will use complete cases. Sensitivity analyses using multiple imputation may be performed for exploratory clinical outcomes, but the results will be interpreted with caution given the small sample size.

*Adherence*

Adherence will be assessed based on three components:(a)use of the digital agenda on at least 80% of intervention days (over 6 weeks),(b)completion of at least 80% of scheduled online training activities, and(c)attendance at 100% of planned videoconference sessions.

Adherence will be reported as the proportion of participants meeting these criteria.

*Intervention Fidelity*

Fidelity will be ensured through a structured process: all occupational therapists delivering the intervention will complete a 20-h training course prior to implementation, covering theoretical foundations, intervention procedures, and use of digital tools. Fidelity will be monitored using session checklists, regular supervision meetings, and ongoing remote support. Fidelity will be categorized as high (≥80% of protocol elements delivered), moderate (60–79%), or low (<60%).

*Acceptability and Usability*

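### The Recruitment row of Table 3 gives no verdict for uptake from 60% to just under 70%

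*Protocol article*

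**What the plan says.** Section 2.9.2 (Feasibility Outcomes) defines the metric: "Recruitment will be measured as the proportion of eligible participants who consent to participate". It then points to where the decision rule is kept: "Progression criteria for feasibility outcomes are summarized in Table 3 and Figure 2".

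In Table 3 the Recruitment row reads GO at "≥70% of eligible approached", AMEND at 50–59% and STOP at <50%. The note under the table allows three verdicts and no residual one: "GO = criteria met for progression to definitive trial; AMEND = criteria met with modifications; STOP = criteria not met". The same note describes the success thresholds as predefined.

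Section 2.7 (Sample Size) fixes the enrolment target: "The planned sample size is 30 children/adolescents". It justifies that number "without requiring a formal calculation of statistical power". The article gives neither an expected uptake nor a planned number of families to approach.

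**The concern.** A three-way progression rule should give every possible result exactly one verdict. The Recruitment row does not: between the top of AMEND (59%) and the bottom of GO (70%) lies a band about ten points wide with no verdict.

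If the observed uptake falls there, the label has to be chosen once the result is known, and a criterion presented as predefined then no longer is. Recruitment is one of the named feasibility outcomes, and the Conclusions say the findings will inform the decision on a randomised trial. The choice between going ahead as planned and going ahead with modified recruitment therefore matters. Section 2.1 also defers full registration until the feasibility outcomes have been analysed, so this table is the main record of the rule that a reader can see.

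**Working it through.** The plan computes no figure here, so there is nothing to reproduce. The checks are whether the bands cover the whole scale, which results fall outside them, and how often that could happen.

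**1. Coverage.** Whole-percent limits from Table 3:

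| Row | GO | AMEND | STOP | Uncovered whole percents |
|---|---|---|---|---|
| Recruitment | ≥70 | 50–59 | <50 | 60 to 69 |
| Retention | ≥80 | 60–79 | <60 | none |
| Data completeness | ≥80 | 70–79 | <70 | none |
| Fidelity | ≥80 | 60–79 | <60 | none |

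The Dropouts row (GO ≤20%, AMEND "21–29% dropout rate", STOP ≥30%) also runs on without a break. Adherence is left out of the comparison because its GO cell includes videoconferences while its AMEND and STOP cells do not.

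**2. Results in the gap at the planned sample size.** Input: 30 consents (section 2.7). Uptake = 30/N, where N is the number of eligible families approached.

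| N | 30/N | Verdict |
|---|---|---|
| 42 | 71.4% | GO |
| 43 | 69.8% | none |
| 46 | 65.2% | none |
| 50 | 60.0% | none |
| 51 | 58.8% | AMEND |
| 60 | 50.0% | AMEND |
| 61 | 49.2% | STOP |

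Every N from 43 to 50 has no verdict. Rounding uptake to a whole percent would move only N = 43 (to 70%, GO); 44 to 50 would stay uncovered.

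**3. Chance of landing in the gap.** This needs two quantities that the article does not give, so both are assumptions: 45 families approached, and true uptake p between 50% and 80%. With X ~ Binomial(45, p), the gap is 0.60 ≤ X/45 < 0.70. That is X = 27 to 31, since 26/45 = 57.8%, 27/45 = 60.0%, 31/45 = 68.9% and 32/45 = 71.1%. So P(no verdict) = P(X ≤ 31) − P(X ≤ 26).

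As a check on the sampling scheme, the last column lets families be approached until 30 consent. N is then negative binomial, and the gap is N = 43 to 50.

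| True uptake p | 45 approached | Until 30 consent |
|---|---|---|
| 50% | 0.11 | 0.10 |
| 55% | 0.28 | 0.26 |
| 60% | 0.48 | 0.48 |
| 65% | 0.56 | 0.57 |
| 70% | 0.44 | 0.46 |
| 75% | 0.21 | 0.23 |
| 80% | 0.05 | 0.06 |

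The two schemes agree closely. If true uptake equals the GO limit of 70%, the rule returns no verdict a little under half the time.

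**The case against.** The other side has several fair points.

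- **The gap is limited.** A reader might infer that the whole progression rule breaks down. The documents do not support that. The STOP limit is intact, so no result in the gap can be taken for a decision not to proceed. Recruitment is one of eight domains. A result of 60–69% misses GO and is above STOP, so AMEND is the natural reading. All of this stands, but that reading is nowhere written.
- **The probabilities depend on assumptions.** A reader might also infer that the trial is likely to land in the gap. With no stated expected uptake, that cannot be said. The chance peaks when true uptake lies in the gap and falls to about 0.05 at 80%. This stands, which is why the whole range is shown.
- **Other rows have small gaps too.** A mean SUS of 67.5, or fidelity of 79.5%, also lies between two printed limits. That is whole-number spacing and disappears on rounding. It is no defect of the same kind and does not support the point.
- **Figure 2 is not visible in the text available.** It may state a recruitment band. If it covers 60–69%, it would differ from Table 3 and the two would need reconciling; Table 3 would still be wrong as printed.
- **It may be a single mistyped limit.** That is plausible, but the article does not show which limit. Reading AMEND as 50–69% or GO as ≥60% would each close the gap, with opposite verdicts for 43 to 50 approached.

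**Conclusion.** The point holds: the Recruitment row of Table 3 is wrong as written. Uptake from 60% to just under 70% has no verdict, and nothing in the visible text provides one. That much, and the range of 43 to 50 approached at 30 consents, follows directly from the protocol's own numbers. The chance of its mattering depends on the assumed 45 approached and the true uptake: roughly one in two for uptake of 60–70%, about 0.1 at 50% and 0.05 at 80%. The consequence is an unplanned choice between GO and AMEND in one domain.

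**What to change.** Close the Recruitment bands in Table 3 before any data are seen. Keeping the printed GO limit of ≥70% and following the pattern of Retention, Data completeness and Fidelity, the AMEND cell becomes 50% to <70%. With 30 consents the rule would then give GO for up to 42 approached, AMEND for 43 to 60 and STOP for 61 or more.

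The sponsor should first confirm that the AMEND limit is the slip. If GO was meant to start at 60%, then 43 to 50 approached would be GO. Figure 2 should be checked against the corrected row.

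As optional tidying, write every row as touching intervals (for example 60% to <80%, or SUS 60 to <68) so that fractional results have a verdict without a rounding rule.

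The cost is one table cell, with no extra data collection or analysis.

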#### 2.4.4. Delivery Format and Dosage

The program will be delivered entirely in a digital, remote format over six weeks. Participants will engage in scheduled online training activities, utilize the digital agenda for planning and organization, and attend synchronous videoconference sessions led by trained occupational therapists. The six-week protocol comprises 12 child/adolescent sessions (two per week) and six parent/teacher sessions (one per week), aligning with the dosage planned for the subsequent randomized controlled trial. In addition to scheduled sessions, participants will be instructed to use the collaborative agenda daily (seven days per week) throughout the intervention to support continuous engagement and transfer of strategies to natural home–school contexts.

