In contrast to the assumption that family involvement in DiverAcción is primarily psychoeducational, the protocol incorporates active family mediation and routine-based practice throughout the intervention period. Parents are required to support regular use of the platform and the collaborative agenda, establish consistent daily routines (e.g., homework, personal care, organization of materials), and apply executive and self-regulation strategies in the home context. These aspects are explicitly addressed during scheduled videoconference sessions with parents, where goal setting, supervision strategies, environmental structuring, and family stress management are discussed and adapted as needed. Importantly, family-mediated change is not only encouraged but also monitored through a multi-informant assessment strategy, including parent-, teacher-, and self-reported measures of executive functioning, emotional regulation, time management, parental stress, and perceived parental competence. This approach allows indirect monitoring of family-level and contextual changes over time.

Nevertheless, DiverAcción differs from highly manualized programs such as Cog-Fun and POET in that family-mediated practice is embedded within a flexible, digitally supported framework rather than prescribed through standardized homework protocols with formal fidelity checklists. This distinction should be considered when interpreting generalization processes and highlights an area for further refinement in future controlled trials.

A notable difference from Teen Cog-Fun is the intensity of family involvement. Whereas Teen Cog-Fun includes only two sessions for parents, DiverAcción provides six dedicated sessions (within an eight-session structure) for parents and teachers. It is reasonable to assume that two sessions may not be sufficient to address the substantial parental challenges of raising an adolescent with ADHD, as suggested by Theule et al. [76], who reported lower satisfaction regarding parents’ own achievements in parental self-efficacy. This expanded involvement in DiverAcción aims to strengthen parental competence and reduce stress through ongoing guidance and interactive support mechanisms.

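### The adherence row of Table 3 sets no cut-off for the proportion that section 2.9.2 reports, and it leaves good agenda and training use with a missed videoconference unclassified

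*Protocol article*

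**What the plan says.** Section 2.9.2 (Adherence) lists three components for each participant:

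- agenda: "use of the digital agenda on at least 80% of intervention days (over 6 weeks");
- training: "completion of at least 80% of scheduled online training activities";
- videoconferences: attendance at all of those planned.

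It then names the result to be reported: "Adherence will be reported as the proportion of participants meeting these criteria".

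The adherence row of Table 3 reads as follows:

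- GO: "≥80% agenda & training; 100% videoconferences"
- AMEND: "60–79% agenda/training"
- STOP: "<60% agenda/training"

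The opening of section 2.9 justifies the 80% and 100% levels by the degree of engagement wanted. The note to Table 3 traces the 80% to a benchmark for session completion. The abstract, section 2.4.8, the Discussion and Table 1 all give two scheduled videoconferences; section 2.4.8 and Table 1 place them in weeks 1 and 3.

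**The concern.** Two things do not fit.

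First, 2.9.2 will produce one number, the share of children who are adherent. Table 3 has no band for that number. Its percentages are the levels that make a single child adherent, carried over as if they were the study result. A reader could apply them to group averages, to the share of children meeting each rule, or to the share meeting all three.

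Second, the videoconference condition stands only in the GO cell. If it fails while agenda and training succeed, the row gives no answer.

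Table 3 is the predefined basis for going on to a randomised trial. If the row can be read in several ways, or is silent on a likely result, the adherence decision will be made after the data are seen.

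A smaller matter: attendance at the six weekly parent/teacher sessions, which have their own row in Table 1, is not a named component of the adherence rule.

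**Working it through.** The plan gives no computed adherence figure, and its sample size is explicitly not based on power, so there is nothing to reproduce. The check is of logic and consequence.

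**Inputs from the document.** 30 children (section 2.7); 6 weeks × 7 days = 42 agenda days; 12 training sessions; 2 scheduled videoconferences per child, so 30 × 2 = 60 calls.

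**Assumed input.** Attendance probability p per call, independent across calls. The document gives no rate; the range used is 0.90 to 0.995.

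**Step 1: the rules work at child level.** 0.80 × 42 = 33.6, so a child needs at least 34 agenda days. If training is counted in sessions, 0.80 × 12 = 9.6, so at least 10. These classify a child. They do not say how many of the 30 children must qualify.

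**Step 2: the reading changes the verdict.** Suppose 20 children are at 95% and 10 at 60% on both agenda and training.

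- Group mean: (20 × 95 + 10 × 60) / 30 = 2500 / 30 = 83.3%, which is GO level.
- Share of children at 80% or more: 20 / 30 = 66.7%, which is AMEND level if the same bands were applied to it.

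**Step 3: the unclassified outcome.** Take agenda and training both at 80% or more, with one of 60 calls missed. Attendance is 59 / 60 = 98.3%, and 29 / 30 = 96.7% of children attended both calls.

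- GO fails, because videoconferences are below 100%.
- AMEND does not apply, because agenda and training are not between 60% and 79%.
- STOP does not apply, because neither is below 60%.

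This holds whether the percentages are averages or shares of children. It also holds on the kindest reading of the slash in the AMEND and STOP cells, where the worse of agenda and training decides.

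**Step 4: how easily the gap is reached.** With the 100% read at study level, P(at least one miss) = 1 − p^60.

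| p per call | p^60 | P(at least one miss) |
|---|---|---|
| 0.90 | 0.002 | 99.8% |
| 0.95 | 0.046 | 95.4% |
| 0.98 | 0.298 | 70.2% |
| 0.99 | 0.547 | 45.3% |
| 0.995 | 0.740 | 26.0% |

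These are the chances of falling into the gap given that agenda and training are otherwise at GO level.

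**The case against.** The best defence is that the row still works over much of its range. If its percentages are read at study level, agenda or training below 80% gives AMEND or STOP whatever the videoconference attendance. That is right. A reader might infer that the criterion can never return a verdict, and the document does not support that. The gap is confined to agenda and training both at 80% or more, which is where GO is decided.

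Figure 2 is also cited for the progression criteria and is not shown. It might carry a cut-off for the proportion, so the first limb is limited to the text and Table 3. It would not change the AMEND and STOP cells.

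Three other stronger readings are tempting and should not be pressed.

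- *Eight videoconferences instead of two.* Section 2.4.4 has participants "attend synchronous videoconference sessions led by trained occupational therapists" without a number, and the Discussion speaks of "six dedicated sessions (within an eight-session structure"). But wherever videoconferences are counted the figure is two. No section says that the six parent/teacher sessions are held by videoconference, and six sessions plus two calls also makes eight.
- *GO with no parent or teacher taking part.* Table 1 includes parents and teachers in the two calls that count for GO, and the feasibility row of Table 2 lists platform metrics for them. What stands is only that attendance at their six sessions is not a named component.
- *GO is practically unattainable.* This needs a strict study-level 100% and an assumed rate. At 99% attendance, all 60 calls are attended with probability 0.55. Misses may also cluster within families, which the independence assumption ignores.

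Finally, the study is descriptive and adherence is one of eight domains in Table 3. That lowers the severity. It does not make the row consistent with 2.9.2.

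**Conclusion.** The point holds in two parts, both on the printed text.

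1. The quantity reported under 2.9.2 has no GO, AMEND or STOP cut-off in the text or Table 3, and the choice between a group mean and a share of children can move the result from GO level to AMEND level (83.3% against 66.7% in the example).
2. Agenda and training at 80% or more with any missed videoconference belongs to no column.

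The second part needs no assumption. Its likelihood does: 95%, 70% and 45% at attendance of 95%, 98% and 99% rest on assumed rates, independent calls, two calls per child and a study-level 100%.

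This is a defect in a stated decision rule, not missing detail. It should be fixed, but it does not undermine the study.

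**What to change.** Keep the per-child definitions. Base the Table 3 verdict on the same quantity that 2.9.2 reports, with all enrolled children as denominator. State the denominator, because 2.9.2 otherwise uses complete cases for the primary feasibility analyses. There are two ways to do this.

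- **Joint.** Set the bands on the share of children who meet all three rules.
- **By component.** Change 2.9.2 to report the share meeting each rule, and let the lowest of the three decide.

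Either could use the 80% and 60% limits that Table 3 already has for retention and fidelity: GO at 80% or more, AMEND from 60% to below 80%, STOP below 60%. With 30 children these are at least 24, 18 to 23, and at most 17.

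The joint version is the stricter. If each child met the agenda and training rules with probability 0.90 each and attended each call with probability 0.95, all independent, the joint share would be 0.90 × 0.90 × 0.95² = 0.73 and the chance of at least 24 of 30 would be 0.27. With 0.95 for agenda and training it would be 0.95 × 0.95 × 0.95² = 0.81, and the chance 0.68. These inputs are assumptions, shown only to inform the choice.

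Under either version, cover videoconferences in all three columns and state that the two scheduled calls (weeks 1 and 3) are the ones counted. Attendance at the six parent/teacher sessions can be reported alongside, without entering the verdict.

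The cost is an edit to one table row and a few sentences. The numerical bands are a judgement for the investigators, to be fixed before data are seen.
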